#### Explanation for the choice of comparators

As the current study aims to explore the feasibility and effectiveness of a novel intervention, we have chosen usual care as the comparator. In a further, fully powered trial aiming to assess the efficacy of the MoNoPol-Sleep intervention, optimized usual care might be chosen as comparator.

#### Criteria for discontinuing or modifying allocated interventions

Not applicable for this non-pharmacological intervention, but nursing homes can leave the study at any time and may withdraw consent.

#### Strategies to improve adherence to interventions

To ensure involvement and adherence of participating nursing homes the research team will provide interested nursing homes with comprehensive information about the study that is specific for the target group. The short intervention period of 16 weeks allows the nursing homes to be closely monitored during data collection and intervention delivery. After completion of the follow-up survey, the control group will receive one to two hours’ training on complex interventions for sleep promotion in people with dementia and will also be provided with corresponding information material developed for the intervention group.

#### Relevant concomitant care permitted or prohibited during the trial

The MoNoPol-Sleep intervention does not replace any part of health care. In order to promote the sleep of people with dementia, the intervention raises awareness, knowledge and skills of nursing home staff with regard to sleep promotion. Furthermore, the current sleep-relevant practices and processes within the nursing home will be reflected.

#### Provisions for post-trial care

Not applicable (see adverse event reporting and harms).

### Outcomes

To investigate the intervention effects, quantitative measurements will be used to measure variables regarding people with dementia and nursing staff. Table 2 summarizes all the outcome instruments.

**Table 2 Tab2:** Outcome instruments

People with dementia				
Variable	Instrument	Source	Measurement points	Type of variable
Demographic variables (e.g. documented sleep apnea, documented dementia diagnosis, Dementia Screening Scale, length of stay in nursing home)	Single items	Nursing records	T0	Inclusion and exclusion criteria
Demographic Variables (e.g. age, sex, care dependency level^a^)	Single items	Nursing records	T0	Control variables
Sleep Disorders	Sleep Disorder Inventory [32]	Retrospective rating by registered nurse (night shift)^c^	T0, T1, T2	Primary outcome, Inclusion criterion
Objective Sleep Measures^b^	Algorithm to analyze actigraphic data with respect to sleep patterns [41, 42]	Actigraphy	T0, T2	Secondary outcome
Quality of Sleep	Pittsburgh Sleep Quality Index [43]	Self-rating by participating people with dementia^d^	T0, T2	Secondary outcome
Daytime Sleepiness	Essener Questionaire of Age and Sleepiness in the Elderly (EFAS) [44]	Retrospective rating by registered nurse (day shift)	T0, T2	Secondary outcome
Quality of Life	QUALIDEM 2.0 [45, 46]	Retrospective rating by registered nurse (night shift)^c^	T0, T2	Secondary outcome
Agitation	Cohen-Mansfield Agitation Inventory [47]	Retrospective rating by registered nurse (day shift)^b^	T0, T2	Secondary outcome
Accidental falls	Single item	Nursing documentation	T1, T2	Control variable
Physical restraint use	Single item	Nursing documentation	T1, T2	Control variable
Psychotropic medication	Single items	Nursing documentation	T1, T2	Control variable
**Staff**				
**Variable**	**Instrument**	**Source**	**Measurement** **points**	**Type of variable**
Demographic variables (e.g. age, sex)	Single items	Staff questionnaire	T0	Control variable
Nurses sleep-related distress	Sleep Disorder Inventory [32]	Retrospective rating by registered nurse (night shift)	T0, T1, T2	Secondary outcome
Nurses distress caused by residents’ challenging behavior	Residents’ Challenging Behavior–related Distress Index [17]	Retrospective rating by registered nurse (day & night shift)	T0, T2	Secondary outcome
		**Cost analysis**		
**Variable**	**Instrument**	**Source**	**Measurement points**	**Type of variable**
Costs related to the implementation of the intervention and the predefined outcomes	Self-developed cost protocol [48]	Documentation by trained external study assistants	Ongoing	Cost outcome

^a^Care levels based on the assessment of the experts of the medical service of the health insurance funds

^b^Only subgroup of eight nursing homes of the Lübeck Study Centre

^c^Retrospective assessment (of the last 2 weeks before data collection) by nursing professionals. Here, the nursing professionals are instructed by a member of the scientific team

^d^Self-assessment = people with dementia guided by a member of the research team

T0 = baseline before randomization, T1 = follow-up after 8 weeks, T2 = follow-up after 16 weeks

For the process evaluation, quantitative data from nursing home managers, staff and the process documentation (intervention delivery and implementation) as well as qualitative staff interviews (individual and focus group interviews) will be assessed (Table 3).

**Table 3 Tab3:** Process evaluation: data collection methods

Parameter	Material	Measurement points	Elements of process evaluation
Recruitment description	▪ Documentation of the recruitment process ▪ Survey of reasons for participation (nursing home management/nursing service management) ▪ Survey of reasons for non-participation/withdrawal (nursing home management/nursing service management)	T0	Recruitment
Description of the context factors of the nursing homes	▪ Existence of concepts or standards for dealing with sleep or promoting sleep (structured survey, nursing service management)	T0, T2 (only control group)	Description of the cluster (Context)
	▪ Culture in the nursing homes (Organizational Readiness for Implementing Change (ORIC)) [49]. ▪ Person-centered care (Person-centered climate questionnaire (staff version) (PCQ-S)) [50]. ▪ Team effort (Assessment of Interprofessional Team Collaboration Scale (AITCS)) [51]. ▪ Sample: nursing services and residential area managers, as well as 20% of all nursing staff per cluster	T0, T2	
Implementation of the intervention components	▪ Information about the needs assessment for each cluster (e.g. number of stakeholders involved, content) ▪ Number, frequency and content of the different components delivered to each cluster (including duration, number and function of participants, topics, necessary adjustments (type, reasons), deviations from the protocol), i.e.: ▪ Educational courses (basic and advanced) offered per cluster ▪ Workshops offered per cluster ▪ Training and support delivered to the change agents ▪ Other components offered	Implementation phase, T1, T2 (only intervention group)	Implementation of the intervention (Delivery)
Adoption of the intervention components in the nursing homes	▪ Content of the sleep-related care concept (document analysis)	T1, T2	Implementation of the intervention (Response)
	▪ Number (rate) of participants attending the workshops per cluster (documentation)	Implementation phase	
	▪ Number of workshops and internal training planned and carried out in the context of the intervention	T1, T2	
	▪ Changes in procedures and processes as a result of the interventions’ implementation (e.g. assessments)	T1, T2	
Change processes in the nursing homes	▪ Changes in procedures and processes due to the implementation of the sleep concept in each cluster (planned vs. implemented)	T1, T2 (only intervention group	
	▪ Changes regarding sleep promotion in the care plans of people with dementia (document analysis, *n* = 5 residents with sleep problems per cluster)	T2 (only intervention group)	
	▪ Performance of care plans for sleep promotion (participating observations, 2 residents with sleep problems from selected nurses (2 per cluster))	T2 (only intervention group)	
	▪ Perception of changes in sleep promotion from people with dementia or their representatives, relatives or legal guardians (interviews, 4 per cluster)	T2 (only intervention group)	
Inhibiting / promoting factors and contextual conditions	▪ Perspective of the target groups (managers, nurses actively involved in the intervention; interviews)	T2 (only intervention group)	

T0 = baseline before randomization, T1 = follow-up after 8 weeks, T2 = follow-up after 16 weeks

Data collection will take place before randomization and intervention implementation (T0, baseline), then again after 8 weeks of intervention (T1, Follow-Up) and after completion of the intervention at 16 weeks (T2, Follow-Up). Process and cost data will be collected ongoing throughout the trial and after completion of the intervention (Fig. 1).

#### Primary outcome

The primary endpoint of the MoNoPol-Sleep trial is the prevalence of at least two sleep problems in people with dementia within the last 2 weeks, assessed with the Sleep Disorder Inventory (SDI) [32]. This instrument (SDI) is based on the Neuropsychiatric Inventory Nursing Home (NPI-NH) [32] and describes the frequency and severity of sleep problems by querying the following sleep problems (German version): (1) “Difficulty falling asleep”, (2) “Getting up in the night”, (3) “Walking around, walking up and down or engaging in inappropriate activities at night”, (4) “Waking up at night, getting dressed with the intention of going outside, thinking that it is morning and it is time to start the day”, (5) “waking up too early in the morning”, (6) “sleeping excessively during the day”, and (7) “other nocturnal behaviors that disturb you”. The presence of these sleep problems is assessed as “yes” or “no” respectively. This allows the detection of existing sleep problems (primary endpoint). Possible missing values will be interpreted as “No”.

Furthermore, the sleep problems are assessed in terms of their frequency and severity. A total value between 0 and 84 is formed by multiplication of frequency and severity data. Higher values correspond to more severe sleep problems (secondary endpoint). The proxy-assessment of sleep problems using Sleep Disorder Inventory (SDI) [32] is carried out exclusively by nurses who have done at least three night shifts in the last 14 days. These nurses will assess their own burden caused by the sleep problems of people with dementia, based on a five-level response scale from “not at all” to “very severe” of the SDI. The burden of the nurses measured in this way is a secondary endpoint in the present study.

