2.	**Implementation of two “sleep nurses” as change agents per nursing home.** ▪ During the intervention phase, the sleep nurses (one nurse from the day shift and one nurse from the night shift) act as contact persons, multipliers, coordinators, change agents and as implementers of person-centered sleep promotion. ▪ For this purpose, the sleep nurses receive in-depth knowledge about sleep promotion, implementation strategies with regard to the MoNoPol-Sleep interventions and problem-solving strategies. ▪ In addition, the sleep nurses can reflect on their actions in coaching sessions and develop new problem-solving strategies.	▪ Local praxis development champions are a crucial factor to implement person-centered care interventions [34, 35] ▪ Sleep nurses are important as contact persons, change agents and local champions. Such champions are recommended for the implementation of complex interventions [36].	▪ Written education material ▪ Written profile of the sleep nurses	▪ Education sessions (both sleep nurses together for each nursing home) ▪ Coaching sessions (both sleep nurses together for each nursing home)	▪ Research staff	▪ Education: approx. Two hours of education as part of component No. 3 ▪ Coaching: approx. One hour after each workshop of the components No. 4 and 5

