4.	**Advanced education course for nursing staff: “Tailored problem solving” (two workshops).** ▪ Two workshops which aim to support the implementation of person-centered sleep promotion and problem-solving competencies. ▪ In both workshops, one case of a resident with sleep problems from the facility will be discussed and solutions for improved sleep promotion sought. ▪ Each workshop contains the following seven steps: (1) Introduction, (2) Presentation of one resident as a case with sleep problems by the sleep nurse, (3) Prioritizing of care problems by all workshop participants, (4) Information about potential reasons for sleep problems by the moderating researcher, (5) Analysis of potential influencing factors for case-specific sleep problems by all workshop participants, (6) Formation of hypotheses for understanding, (7) Development and consensus on an action plan.	▪ Based on a theory of change which was developed during the MoNoPol-Sleep intervention development: Sleep problems and their causes are individual for each person with dementia. ▪ Nursing home staff needs support in problem solving which take the available resources of people with dementia and the care environment into account. ▪ The seven steps of the workshop are based on the available knowledge for conducting case conferences [38–40].	▪ Direction plan for the workshop ▪ Digital presentation ▪ Written education material ▪ Self-developed, standardized case analysis chart ▪ Moderator manual including e.g. list of causes for sleep problems, list of symptoms of sleep problems)	▪ Group sessions	▪ Research staff ▪ Sleep nurses	▪ Both workshops take approx. 1.5 h each ▪ The first workshop will be held after component No. 3 and by the 6th week of intervention at the latest ▪ The second workshop will be held between the 7th and 12th week of intervention

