### Assignment of interventions: blinding

#### Who will be blinded

Due to the type of intervention, it is not possible to blind the nursing home staff and members of the research team who are carrying out the intervention and the data collection. However, the member of the research team entering the data in the database and also the biostatistician doing the data analysis will be blinded with regard to group allocation (neutral group IDs) of clusters and people with dementia.

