### Data collection and management

#### Plans for assessment and collection of outcomes

The outcome instruments were chosen based on their appropriateness and feasibility for the study aim, setting and population as well as their psychometric properties (validity and reliability). The majority of the instruments are proxy-based. Nurses who have a high level of knowledge about the participating people with dementia and their care during day and night (24 h) will carry out the proxy assessment. Proxy-rating nurses have to work regularly in day and night shifts and/or take part in the handover between day and night shifts. In addition, the extent of their regular weekly working time must be at least 50%.

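### A sleep nurse who delivers the intervention can also qualify as a rater of the primary outcome, and no rule in the protocol prevents it

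*Protocol article*

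**What the plan says.** **Who delivers.** Table 1, component 2, appoints two sleep nurses per home, "one nurse from the day shift and one nurse from the night shift", and describes them as "change agents and as implementers of person-centered sleep promotion". The research team trains and coaches them. Components 4 and 5 list them beside the research staff as intervention providers. The steps of the component 4 workshops include "Presentation of one resident as a case with sleep problems by the sleep nurse".

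**Who rates.** Under Primary outcome, the SDI proxy rating "is carried out exclusively by nurses who have done at least three night shifts in the last 14 days". Table 2 names a registered night-shift nurse as the source for SDI and QUALIDEM, and a registered day-shift nurse for CMAI and EFAS. The section on assessment and collection of outcomes adds good knowledge of the resident, at least half-time working hours, and this: "Proxy-rating nurses have to work regularly in day and night shifts and/or take part in the handover between day and night shifts". The nurse-level eligibility criteria set minimum contract hours and night shifts. None of these places mentions sleep nurses or intervention providers.

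**Who is blinded.** The blinding section says "it is not possible to blind the nursing home staff and members of the research team" who carry out the intervention and collect the data. Only data entry and the biostatistician are blinded.

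**The concern.** The primary endpoint is the presence of at least two SDI problems, each a retrospective yes/no judgement by a nurse who knows the allocation. Every resident enters with at least two problems, so for a resident with exactly two, one changed answer turns a case into a non-case.

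The protocol discloses that staff are unblinded. It does not address the overlap of two roles. The rater rule selects night-shift nurses who know the resident, and one of the two people appointed to make the intervention work in each intervention home comes from the night shift. Sleep nurses exist only in that arm and only after the baseline rating, which precedes randomisation. Self-rating by a provider is therefore possible only at T1 and T2 and only in one arm. Blinding the analyst does not touch an error already present in the recorded data.

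**Working it through.** **Step 1. Compare the two roles.**

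| Rater criterion for SDI | Place | What is said of the night-shift sleep nurse |
|---|---|---|
| Registered nurse, night shift | Table 2 | Night shift: yes. Registered: not stated |
| At least three night shifts in the last 14 days | Primary outcome | Not stated, but plausible for a night-shift nurse |
| Day and night work and/or handover; at least half-time; knows the resident | Assessment and collection of outcomes | Not stated |
| Not an intervention provider | Nowhere | No such rule |

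So the sleep nurse *can* meet the criteria; the text does not guarantee it. The same comparison applies to QUALIDEM (night-shift rater) and, for the day-shift sleep nurse, to CMAI and EFAS.

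**Step 2. Reproduce the planned power.** Inputs from the sample size section: 80% versus 61%, ICC 0.05, 12 homes of 15 residents per arm (180), alpha 5%. The test is two-sided (statistical methods section).

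- Design effect = 1 + (15 − 1) × 0.05 = 1.70; effective n per arm = 180 / 1.70 = 105.9.
- Pooled SE, with mean proportion 0.705: √(2 × 0.705 × 0.295 / 105.9) = 0.0627. Unpooled SE: √((0.80 × 0.20 + 0.61 × 0.39) / 105.9) = 0.0613.
- Power = Φ((0.19 − 1.96 × 0.0627) / 0.0613) = 86.3% (stated: 85%).
- With 10% dropout, 13.5 per home: design effect 1.625, effective n 99.7, power 84.2% (stated: 84%).

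The sample size reproduces and is not in question.

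**Step 3. Rejection rate with no true effect.** Assume a true prevalence of 80% in both arms and a recorded prevalence in the intervention arm lowered by d. With effective n = 105.9, SE = √((0.80 × 0.20 + p(1 − p)) / 105.9), p = 0.80 − d, and the two-sided rejection probability is Φ(d/SE − 1.96) + Φ(−d/SE − 1.96).

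| d (assumed) | SE | d/SE | Rejection probability |
|---|---|---|---|
| 2 points | 0.0560 | 0.357 | 0.065 |
| 5 points | 0.0573 | 0.873 | 0.141 |
| 10 points | 0.0591 | 1.692 | 0.394 |

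**Step 4. What produces such a shift.** If sleep nurses rate a share s of intervention-arm residents and record a fraction f of true cases as non-cases, then d = 0.80 × s × f, so f = d / (0.80 × s).

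| d | f if s = 0.25 | f if s = 0.50 | f if s = 1 |
|---|---|---|---|
| 2 points | 10% | 5% | 2.5% |
| 5 points | 25% | 12.5% | 6.25% |
| 10 points | 50% | 25% | 12.5% |

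The documents give neither s nor f. The 10-point shift needs half of the sleep nurse's cases reversed if she rates a quarter of the residents, but only one in eight if she rates all of them.

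**The case against.** **Silence in a condensed article.** Which nurse rates which resident could be settled in the full protocol or in the operating procedures that the data management section mentions. This carries some weight: nothing says that sleep nurses will rate. But rater eligibility is not left open here. It is set out at nurse level, in Table 2, under the primary outcome and in the data collection section. A plan that follows those rules as written admits the provider.

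**Direction.** A reader might infer that the bias must favour the intervention. The documents do not support that certainty. The posters in component 6 teach the identification of sleep problems, and the component 4 moderator manual lists their symptoms, so a trained nurse may tick more items. That would work against the intervention: over-recording of 5 points would cut the planned 19-point difference to 14. Either way the error is differential.

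**Disclosure and existing checks.** The lack of staff blinding is admitted, trained research staff supervise the ratings, and PSQI self-ratings and actigraphy do not depend on nurses. These help only in part. The supervising data collectors are unblinded too, the PSQI will not be obtainable from all residents, and actigraphy covers 40 residents at one centre. The trial is called exploratory, which lowers the stakes but does not remove the problem.

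**Project coordinators and changing raters.** A reader might extend the point to the home's project coordinator, or ask that the T0 rater also rate at T2. Neither extension holds. Coordinators exist in every home, in both arms, and the text gives them information and consent tasks only. A compulsory same-rater rule could clash with the 14-day night-shift criterion, since a T0 rater may no longer qualify 16 weeks later.

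**Limited benefit.** The remaining night nurses are unblinded and may have attended the courses. This stands: the change removes the most direct conflict and leaves the general one.

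**Conclusion.** The point holds in a limited form. As written, the rater rules allow a named intervention provider to rate the primary outcome at T1 and T2 in the intervention arm only, and the planned blinding and supervision do not prevent it. The text does not show that sleep nurses will rate, that each of them qualifies, or that the error must favour the intervention; the last is probable, not certain.

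The size cannot be fixed from the documents. The range of about 6% to 39% rejection rests on assumed shifts of 2 to 10 points, no true effect, 80% prevalence, ICC 0.05 and full follow-up of 180 residents per arm. At the low end the harm is small; at the high end the spurious shift is about half of the planned 19 points. The design remains sound, but a positive primary result would be open to the objection that providers scored their own work. The rule should be added.

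**What to change.** Add to the primary outcome section and to the section on assessment and collection of outcomes:

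> *Sleep nurses do not rate SDI, QUALIDEM, CMAI or EFAS at T1 or T2. Each home names its eligible raters before randomisation, and sleep nurses are chosen from other staff where staffing allows. Rater ID is recorded at each time point.*

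Where a home has no other eligible rater, record the exception and obtain the rating anyway. It must not be left blank, because the primary outcome section counts missing SDI values as absence of the problem, which would itself lower recorded prevalence in the intervention arm.

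Add a sensitivity analysis of the primary outcome that excludes any T2 rating made by a sleep nurse. It should be supportive only, since it selects residents on something that arises after randomisation.

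Cost: one eligibility rule and one field on the case report form. Naming raters in time is feasible because recruitment and baseline data collection precede allocation. The downside is a smaller rater pool, in intervention homes only, which will be felt most where night nurses are few. Bias from the other unblinded, trained nurses remains and should be acknowledged when the results are reported.
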